#### Body mass index and weight status

Height and weight will be measured using a standard protocol. Height will be measured to the nearest 1 mm using a calibrated portable stadiometer (Seca 213, Hamburg, Germany)). Weight will be measured to the nearest 0.1 kg using a calibrated portable digital scale (Tanita Corporation, IL, USA). BMI will be calculated as body weight in kilograms divided by height in meters squared. BMI will be converted to age- and sex-specific percentiles or z-scores using the World Health Organization Growth Standards for 0 to 5 years [33].

### Secondary outcomes

#### Parental self-efficacy

Parental confidence in relation to promoting healthy eating, reducing sedentary time, and promoting physical activity will be assessed using an established tool from the Infant study [34]. The scale comprises 20 items addressing four parenting domains: 1) self-efficacy for promoting healthy eating; 2) self-efficacy for limiting non-core foods; 3) self-efficacy for promoting physical activity; and 4) self-efficacy for limiting screen use. Responses are recorded on a 5-point scale with endpoints ranging from ‘not at all confident’ to ‘extremely confident’. These scales have established evidence of validity and reliability [34], with internal consistency ranging from 0.72 to 0.85 [35].

#### Parent feeding practices

The Feeding Practices and Structure Questionnaire (FPSQ-28) [36] will be used to measure the following two feeding constructs: ‘Reward for Eating’ and ‘Persuasive Feeding’. Items are scored on a 5-point Likert scale with higher scores indicating greater endorsement of that practice. The FPSQ-28 has been validated with mothers of young children (2–5 years) assessing the effects of an intervention on feeding practices. The two constructs selected for this study show good internal consistency: ‘Reward for Eating’ α = 0.89 and ‘Persuasive Feeding’ α = 0.73 [36].

#### Parental support for physical activity

Parental support for children’s physical activity will be assessed using a 5-item scale developed by Trost et al. [37]. Parents report how often they ‘encourage their child to do physical activities or play sports’; ‘play outside or do physical activity or sports with their child’; ‘provide transportation to a place their child can do physical activity or play sports’; ‘watch their child participate in sport, physical activities or outdoor games’; and, ‘tell their child that physical activity is good for his or her health’. Responses are recorded on a 6-point scale with endpoints ranging from zero (never) to five (daily). In a recent study of Australian 3- to 6-year-olds, the internal consistency of the scale, as measured by Cronbach’s alpha, was acceptable at 0.79 [38].

#### Screen time parenting practices

Two scales from the Physical Activity and Screen Time Parenting Practices Questionnaire [39] will be used to measure screen-related parenting practices: “limiting or monitoring screen time” and “use of screen time to reward/control child behavior.” For the limiting or monitoring screen time scale, parents will rate statements describing how tightly they monitor their child’s screen time on weekdays and weekend days. Responses are recorded on a 5-point scale with endpoints ranging from ‘strongly disagree’ to ‘strongly agree’. For the use of screen time to reward/control child behavior scale, parents report how often they use screen time as a reward for good behavior; take away screen time as punishment for bad behavior; offer additional screen time as a reward; and use screen time to control children’s behavior. Responses are recorded on a 6-point scale with endpoints ranging from ‘never’ to ‘very often’. Both scales have evidence of internal consistency (α = 0.85 to 0.89) and test-retest reliability (ICC = 0.95 to 0.97) [40].

#### Sleep parenting practices

Parenting practices related to sleep will be measured using the consistency scale (5 items) from the Bedtime Routines Questionnaire [41]. Parents will be asked to rate how often: their child slept in the same place, went to bed at the same time; was put to bed by the same person; performed the same activities before going to bed; and performed events in the same order before going to bed. Responses are recorded on a 5-point scale with endpoints ranging from ‘almost never’ to ‘nearly always. The bedtime consistency scale has established evidence of internal consistency (α = 0.79 to 0.82) and test-retest reliability (ICC = 0.86) [40].

### Intervention Fidelity

Following each playgroup session in which the intervention is delivered, the facilitator will complete a checklist documenting the essential elements of the program. The checklist will record overall parent attendance, the number of parents engaged in each conversation, approximate time spent in each conversation, the extent to which key messages were delivered as planned, and parents’ level of engagement in the conversations. Facilitators will be able to note the highlights of the session as well as any challenges encountered during the session.

### Overall satisfaction, engagement and perceived utility

At the conclusion of the intervention program, parents will be invited to complete a survey assessing overall satisfaction with the Healthy Conversations @ Playgroup program, engagement with the program, enjoyment of the conversations, and the perceived utility of the group conversations and Facebook posts. Parents will be asked to rate on a 5-point scale their overall satisfaction with the program (not at all satisfied, slightly satisfied, moderately satisfied, very satisfied, extremely satisfied); the usefulness of each of the five healthy conversation topics and associated Facebook posts (not at all, a little, somewhat, mostly, very); how frequently they took part in the conversations (always, usually, about half the time, seldom, never); and enjoyment of the conversations (not at all, a little, somewhat, mostly, a great deal). Parents will also be asked if they would recommend the Healthy Conversations @ Playgroup program to others and comment on their response.

### Statistical analysis

Statistical analyses will follow standard principles for RCTs using two group comparisons including all participants on an intention-to-treat basis. Between-group differences in the primary and secondary outcomes will be tested using a general linear mixed model, which accounts for the clustering of parent-child dyads within playgroups. Within each model, condition, time, the condition by time interaction will be included as fixed effects, with playgroup nested within condition, parent-child dyads nested within playgroup and condition, and the playgroup by time interaction nested within condition included as random effects.

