### Eligibility criteria

Playgroups meeting the following inclusion criteria will be eligible to participate in the program: located within a 150 km radius of the Queensland Centre for Children’s Health Research, Flinders University, South Australia or Telethon Kids Institute, University of Western Australia; operating as a community playgroup (that is, coordinated by parent volunteers rather than a paid facilitator); and at least four parent-child dyads willing to participate in the evaluation of the program. In each participating playgroup, all parents with children between the ages of 1 and 5 years will be invited to participate in the evaluation. Parents with multiple children within the specified age range will be asked to enroll their oldest child in the study. Parents will be excluded if they are unable to give informed consent or have insufficient literacy to complete data collection. Parents with children outside the target age range or children with chronic health conditions that may adversely influence weight status, physical activity, diet, or sleep (e.g., severe respiratory disease, congenital heart disease), will be able to participate in the program, but will be excluded from the evaluation.

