### Sample size and power

For Aim 1, the intervention effect is the net difference for change in the healthy lifestyle behaviors immediately post intervention and at 6-months follow-up. The research hypothesis is that the intervention will result in net differences of 0.5 serving of vegetables (38 g per day), 1.5 servings of discretionary foods per day, 15 min or 2% of time in MVPA, 30 min screen time per day, and 40 min of sleep per 24 h period. The null hypothesis is a net difference of zero. For Aim 2, the intervention effect is the net difference for change in BMI z-score at 6-months follow-up. The research hypothesis is that the intervention will result in a difference of 0.30 BMI z-score units. The null hypothesis is a net difference of zero. For a 2-year-old at the 84th percentile or a BMI z-score of 1.0, a difference of 0.30 z-score units equates to a clinically meaningful reduction of 0.4 kg in excess weight.

Table 2 reports minimal detectable differences for samples of 20, 30, and 40 community playgroups per condition. All calculations were performed assuming a power of 0.80, a 2-tailed alpha level of 0.05, an average cluster size of six parent-child dyads, and an intra-cluster correlation (ICC) of 0.10 and 0.02 for the child health behaviors and BMI z-score, respectively. Standard deviation estimates for vegetable intake were based on dietary intake data from the NOURISH randomized controlled trial [20]. The standard deviations for time in physical activity and screen time were based on previously published studies in Australian children aged 0–5 years [21]. The standard deviation for sleep duration was based on published data on Australian children [10]. The standard deviation for change in BMI z-score was based on data from the NOURISH randomized controlled trial [20]. Based on these calculations, a sample of 30 playgroups per condition achieves ≥80% power to detect the hypothesized between-group differences for each of the primary outcomes. To offset a projected attrition rate of up to 25%, an additional two children within each playgroup will be recruited, providing an overall sample of 60 community playgroups and 480 parent-child dyads.

**Table 2 Tab2:** Minimal detectable differences for child health behaviors and BMI z-score

Study Outcome	Hypothesised Effect	Est. SD	20 Playgroups (***n*** = 120)	30 Playgroups (***n*** = 180)	40 Playgroups (***n*** = 240)
Veg Intake	½ serve, 38 g/d	58 g/d	26 g/d	21 g/d	18 g/d

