### Participant characteristics

Demographic information will be collected at baseline using an online survey and will include child date of birth, child sex, parental age, parental education, and family structure.

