#### Physical activity

The percentage of daily time spent in moderate-to-vigorous intensity physical activity (MVPA) will be measured using the Axivity AX3 accelerometer (Axivity Ltd. Newcastle, United Kingdom). Participants will receive the accelerometer and an information pack via express mail. The pack will include an introductory letter to parents, a detailed instruction sheet, an activity monitoring log sheet to record any activity monitor removals, and a pre-paid padded envelope to return the accelerometer and log sheet to the research team. The child will be asked to wear the accelerometer on their non-dominant wrist 24-h per day for seven consecutive days (except for bathing or water-based activities).

Upon return of the accelerometer via express mail, raw accelerometer data (50 Hz) will be downloaded and processed into physical activity metrics using a random forest physical activity classification algorithm specifically developed for children under five [31]. This validated machine learning algorithm uses 20 features extracted from the raw tri-axial acceleration signal to classify activity type and quantify daily time spent in sedentary activities (sitting or lying down), light-intensity activities and games (slow walking, standing, standing arts and crafts), walking, running, and moderate-to-vigorous intensity activities and games (active games with balls, riding bikes/scooters). In a free-living evaluation, the random forest algorithm exhibited an overall classification accuracy of greater than 80%. MVPA will be calculated by summing daily time spent in walking, running, and moderate-to-vigorous activities and games.

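### The analysis model has no child-age term for children aged 1 to 5 years; adding baseline age and age by time would be a small, nearly free gain in precision for the behavioural outcomes

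*Protocol article*

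**What the plan says.** All places are in the protocol article.

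- **Statistical analysis** gives one model for the primary and secondary outcomes. Fixed effects: "Within each model, condition, time, the condition by time interaction will be included as fixed effects". Besides playgroup, the random part has "parent-child dyads nested within playgroup and condition, and the playgroup by time interaction nested within condition included as random effects". No baseline covariate is named.
- **Eligibility criteria**: "all parents with children between the ages of 1 and 5 years will be invited to participate in the evaluation".
- **Participant characteristics**: the baseline survey "will include child date of birth, child sex, parental age, parental education, and family structure", so exact age is available before randomisation.
- **Sample size and power**, Aim 1: "the intervention effect is the net difference for change in the healthy lifestyle behaviors immediately post intervention and at 6-months follow-up".
- **Physical activity**: "MVPA will be calculated by summing daily time spent in walking, running, and moderate-to-vigorous activities and games". The Sleep section counts both day and night sleep. Neither measure is standardised for age.
- **Body mass index and weight status**: BMI is converted to an age- and sex-specific score against the WHO standards.
- **Randomization, allocation, and blinding**: permuted blocks within site. Child age is not mentioned as a stratifier.

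**The concern.** Follow-up runs from baseline to 6 months after a 10-week programme, about 8 months. Over that time a child of 12 months may well change more in walking, naps and screen use than a child of 4 years. The model fits one time trend to both, and a common trend cannot absorb development that proceeds at different rates at different ages.

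Two things follow. First, age-dependent change is left in the residual. If playgroups differ in the ages they attract, it is also left in the playgroup-by-time term, and intervals are wider than they need to be. Second, if the arms happen to differ in mean age, the estimated difference in change moves by roughly that difference times the age gradient in change. At stake is some precision, and closeness to the truth in the one allocation that is realised. The type I error rate is not at stake.

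**Working it through.** **1. Reproduce the plan's figure.** Inputs from Sample size and power: power 0.80, two-sided alpha 0.05, 6 dyads per playgroup, ICC 0.10 for behaviours, 30 playgroups (180 dyads) per arm. Design effect = 1 + 5 × 0.10 = 1.5.

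SE = SD × √(2 × 1.5 / 180) = 0.1291 × SD, and detectable difference = (1.960 + 0.842) × SE.

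| Outcome | SD (Table 2) | SE | Detectable difference | Table 2 |
|---|---|---|---|---|
| Sleep | 96 min | 12.4 | 34.7 min | 35 |
| Screen time | 75 min | 9.68 | 27.1 min | 27 |
| % time in PA | 5 points | 0.645 | 1.81 points | 1.8 |

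Table 2 is reproduced without any age covariate. Power for the hypothesised effects of the six primary outcomes is 0.85 or more.

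**2. Which part of an age effect reaches the estimate?** Small simulations of the stated model were run (60 playgroups, 6 dyads each, 3 occasions, arms differing by 0.5 year in mean age, six data sets per setting). They show direction only.

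- Age acts on level only (20 units per year), complete data: the mean condition-by-time estimate at T3 is 0.411 both without and with an age main effect. Level differences cancel.
- The same with 25% dropout: adding an age main effect moves the estimate by at most 0.41, against an SE of about 9.
- Change also depends on age (8 units per year): the mean estimate is 1.2 without age and 1.2 with an age main effect. It is −2.0 with age by time. The SE stays at about 8.3 to 8.4. Only the interaction matters.

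**3. Size of the precision gain.** The documents give no age distribution and no gradients, so both are assumed. Ages uniform over 1 to 5 years give an SD of 4/√12 = 1.155 years. The share of variance in change explained by age is R² = (gradient × 1.155 / SD)², and the detectable difference is multiplied by √(1 − R²).

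| Outcome | Gradient in change, per year of age | R² | Detectable difference | Fall |
|---|---|---|---|---|
| Sleep | 5 to 10 min | 0.4 to 1.4% | 34.7 → 34.7 to 34.5 | 0.2 to 0.7% |
| Screen time | 5 to 10 min | 0.6 to 2.4% | 27.1 → 27.0 to 26.8 | 0.3 to 1.2% |
| % MVPA | 0.5 to 0.8 points | 1.3 to 3.4% | 1.81 → 1.80 to 1.78 | 0.7 to 1.7% |

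Two sensitivity checks, taken at the largest case (MVPA, 0.8 points per year):

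- The article does not say that the behavioural SDs are SDs of change. If they are single-occasion SDs and the baseline to follow-up correlation is 0.75 (assumed), the variance of change is 2 × (1 − 0.75) = 0.5 of SD². Then R² = 0.0342 / 0.5 = 0.068 and the fall is 3.5%.
- If playgroups cluster by age with an age ICC of 0.3 (assumed), the SE of the difference in mean age is 1.155 × √(2 × 2.5 / 180) = 0.193 year. The share of the estimate's variance due to age is (0.8 × 0.193 / 0.645)² = 0.057 and the fall is 2.9%.

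Taken together, the range is about 0 to 4%.

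**4. Size of a chance shift.** For an age ICC of 0 to 0.3, the 95% limit for a chance difference in mean age is 0.24 to 0.38 year (1.96 × 0.122 to 1.96 × 0.193). Multiplied by the gradients:

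- Sleep and screen time: 0.24 × 5 = 1.2 min to 0.38 × 10 = 3.8 min, against hypothesised effects of 40 and 30 min.
- MVPA: 0.24 × 0.5 = 0.12 to 0.38 × 0.8 = 0.30 points, against 2.0.

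Even at these limits the shift is at most 0.30 / 0.645, or just under half a standard error, and it is part of what the standard error already covers.

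**The case against.** The strongest reply is that nothing here is wrong. Playgroups are randomised, so the unadjusted contrast is valid. The design reaches its stated power without age, and on low gradients the gain disappears in Table 2's rounding. The article is also condensed: it says which terms will be included, not that no others will be, and covariates are commonly left to an analysis plan, which is not shown here. All of this stands as to size and validity. It does not remove the point, because the article does commit to a specific model for every outcome, and an obvious baseline variable that the trial already holds is not in it.

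A reader might infer three stronger things, none of which the documents support:

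- **That any age imbalance stays in the effect estimate, or that developmental change as a whole becomes noise.** The effect is a difference in change with a dyad random effect. Stable level differences cancel (exactly so with complete data), and average development goes into the time effect.
- **That a chance imbalance is bias.** Under randomisation it is not.
- **That age-driven dropout undermines the likelihood analysis.** The article projects attrition of up to 25% but nowhere ties it to age, and accelerometers go to and from families by post. In the simulation with 25% dropout, including age as a main effect barely moved the estimate.

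**Conclusion.** The point holds as a minor improvement in precision and robustness for vegetables, discretionary foods, MVPA, screen time and sleep. It does not extend to BMI z-score, which is already standardised for age and sex. The stated analysis is valid and the sample size needs no change.

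For the three outcomes worked through, the gain is about 0 to 4% of the detectable difference and nearer 0 to 2% on the Table 2 SDs as they stand. The chance shift it guards against is at most a few minutes a day, or about 0.3 percentage points of MVPA. These figures rest on uniform ages over 1 to 5 years, on the assumed gradients in change, and on the two sensitivity assumptions for the upper end. Gradients were not worked out for the two diet outcomes. At T2, after only 10 weeks, age-dependent change and therefore the gain should be smaller.

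**What to change.** In the Statistical analysis section, state that the models for the five behavioural primary outcomes also include child age at baseline (from date of birth) and its interaction with time as fixed effects, fixed before unblinded data are seen. An age main effect alone would do almost nothing. Leave the BMI z-score model as it is. If an analysis plan already specifies this, a cross-reference is enough.

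The cost is one sentence and no new data. With linear age and three occasions it adds three parameters (one for age, two for age by time) among about 360 completers (60 playgroups × 6). Specifying it now also avoids an adjustment added after an imbalance has been seen, which would look data-driven.

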### Randomization, allocation, and blinding

Group assignment for each site will be completed by an independent statistician using an allocation sequence generated by permuted block randomization. After baseline assessments, playgroups in each site will be randomized to the next condition (intervention or wait-list control) on the list using the database randomization module in the Research Electronic Data Capture (REDCap) platform hosted at The Queensland University of Technology [22]. Trained assessors blinded to group allocation will collect the primary and secondary outcome data. Within a health behavior intervention, it is not possible to blind either the persons delivering the intervention (peer facilitators – see below) or participants; however, peer facilitators will not take part in outcome assessments.

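### The planned condition-by-time contrast leaves baseline free by arm and gives up precision; power for MVPA, screen time and sleep is unverified because Table 2 carries no baseline-to-follow-up correlation

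*Protocol article*

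**What the plan says.** The Statistical analysis section gives the fixed effects of the mixed model: "Within each model, condition, time, the condition by time interaction will be included as fixed effects". The random effects are playgroup, parent-child dyad and playgroup by time. Neither baseline as a covariate nor a shared baseline mean is mentioned.

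Sample size and power defines the target for the behaviours in the same terms: "the intervention effect is the net difference for change in the healthy lifestyle behaviors", both immediately after the intervention (T2) and at 6 months (T3). The BMI z-score effect is likewise a net difference in change, at 6 months. The inputs are given as "All calculations were performed assuming a power of 0.80, a 2-tailed alpha level of 0.05, an average cluster size of six parent-child dyads". The ICC is taken as 0.10 for the behaviours and 0.02 for BMI z-score. The conclusion is that "a sample of 30 playgroups per condition achieves ≥80% power to detect the hypothesized between-group differences for each of the primary outcomes".

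On the SDs, the section says "The standard deviations for time in physical activity and screen time were based on previously published studies". It describes the vegetable and sleep SDs in a similar way, as taken from intake data or published data. Only the BMI z-score SD is called an SD for change. The discretionary-food SD has no stated source.

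Randomization, allocation, and blinding fixes the timing: "After baseline assessments, playgroups in each site will be randomized to the next condition".

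**The concern.** Baseline comes before allocation, so the arms have the same expected baseline mean. A free condition effect at baseline estimates a quantity known to be zero, and its sampling error is carried into every change contrast. With the number of playgroups fixed at 60, this is avoidable loss.

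The power calculation also does not correspond to the contrast it is meant to support. A difference in change needs either an SD of change, or a single-occasion SD together with a correlation. Table 2 uses an SD alone. For MVPA, screen time and sleep the margin between detectable and hypothesised difference is narrow (1.8 against 2.0%, 27 against 30 min, 35 against 40 min), so the unstated correlation decides whether the 80% claim holds.

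**Working it through.** **Inputs.** Sample size and power gives 30 playgroups per arm, six analysed dyads each (180 per arm), and ICC 0.10 (behaviours) or 0.02 (BMI z-score). Table 2 gives the SDs and hypothesised effects. The documents give no baseline-to-follow-up correlation, so r is an assumption and a range is shown.

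**Step 1: reproduce Table 2.** The design effect is DE = 1 + 5 × ICC, which is 1.5 for the behaviours and 1.1 for BMI z-score. The minimal detectable difference is MDD = (1.960 + 0.842) × SD × √(2 × DE/180). For the behaviours the multiplier of the SD is 2.802 × √(3.0/180) = 0.3617; for BMI z-score it is 2.802 × √(2.2/180) = 0.310.

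| Outcome | SD | MDD computed | Table 2 | Hypothesised | Power |
|---|---|---|---|---|---|
| Vegetables, g/d | 58 | 20.98 | 21 | 38 | 99.9% |
| Discretionary, serv/d | 2 | 0.723 | 0.7 | 1.5 | >99.9% |
| MVPA, % | 5 | 1.81 | 1.8 | 2.0 | 87.3% |
| Screen, min/d | 75 | 27.1 | 27 | 30 | 87.3% |
| Sleep, min/d | 96 | 34.7 | 35 | 40 | 89.8% |
| BMI z-score | 0.90 | 0.279 | 0.28 | 0.30 | 85.4% |

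All six values match, with no correlation term in the formula.

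**Step 2: variance of the planned contrast.** With a single-occasion SD, equal variances over time and complete data, the difference in change has variance factor 2(1−r). Adjusting for baseline, or constraining it to be common, gives 1−r². The ratio is 2(1−r)/(1−r²) = 2/(1+r): 1.54 at r = 0.3, 1.33 at 0.5, 1.18 at 0.7. Table 2 matches the planned contrast only where 2(1−r) = 1, that is r = 0.5.

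**Step 3: power if the tabulated SDs are single-occasion.**

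| r | MVPA and screen: change | adjusted | Sleep: change | adjusted |
|---|---|---|---|---|
| 0.2 | 68.8% | 88.5% | 72.3% | 90.9% |
| 0.3 | 74.5% | 90.1% | 77.9% | 92.3% |
| 0.4 | 80.7% | 92.2% | 83.8% | 94.1% |
| 0.5 | 87.3% | 94.7% | 89.8% | 96.1% |
| 0.7 | 97.9% | 99.1% | 98.6% | 99.5% |

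The r at which the change contrast has exactly 80% power is 1 − (effect/MDD)²/2. For MVPA and screen time this is 1 − (1.106)²/2 = 0.388; for sleep, 1 − (1.152)²/2 = 0.336. At r = 0.3 the MDDs become 2.14%, 32.1 min and 41.1 min, each above its hypothesised effect. Even at r = 0, vegetables keep 95% power and discretionary foods 98%.

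**Step 4: which correlation r is.** It refers to playgroup means: r = [6 × ICC × CAC + (1 − ICC) × SAC]/DE, where CAC is the playgroup-level and SAC the child-level autocorrelation. At ICC 0.10 this is 0.4 × CAC + 0.6 × SAC. With SAC = 0.3, CAC of 0.8, 0.5 and 0.3 gives r = 0.50, 0.38 and 0.30.

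**Step 5: correlation pattern over visits (illustration only).** A dyad intercept with independent residuals implies one common correlation between all visits. Suppose the true correlations were 0.7 (T1–T2), 0.6 (T2–T3) and 0.5 (T1–T3), averaging 0.6. At T3 the model SE over the true SE is √(0.4/0.5) = 0.894, so nominal 5% becomes about 8%. At T2 it is √(0.4/0.3) = 1.155, giving about 2.4%.

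**The case against.** The condition-by-time contrast is unbiased under randomisation and matches the stated aim of comparing change. Omitting baseline adjustment is a loss of efficiency, not an error or a contradiction. That is right, and the point is put as an improvement. The article does state its fixed effects, however, so this is a stated choice and not a detail left for later.

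A reader might infer that the trial is underpowered. The documents do not show that. They give no r, and the single-occasion reading of the behaviour SDs is an inference from their wording. Only three of six primary outcomes are exposed. Noise at child level does not by itself make r low: at CAC 0.8, MVPA and screen time fall short only if SAC is below (0.388 − 0.32)/0.6, about 0.11. At CAC 0.5 the corresponding limit is about 0.31. The test-retest ICCs reported for screen time (0.91 to 0.93) and sleep (0.85 to 0.95) do not suggest noisy instruments, though they do not measure stability over 10 weeks or to T3.

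A reader might also take 8% as the trial's actual type I error. It rests on three assumed correlations, and the article does not spell out a residual structure or rule out an unstructured one. Those correlations are also high enough (0.5 or more to baseline) that the power shortfall would not occur, so the two harms should not be added together.

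**Conclusion.** The precision loss stands for any r below 1, and the fix costs almost nothing. The power statement for MVPA, screen time and sleep is unverified. If their SDs are single-occasion, it falls short when r is below about 0.39 (MVPA, screen time) or 0.34 (sleep), whereas baseline-adjusted power never falls below the Table 2 calculation. Vegetables and discretionary foods are not affected. BMI z-score keeps 85% if 0.90 is a change SD, as stated; were it a single-occasion SD, the threshold would be r of about 0.42. Above r = 0.5 the plan has more power than it claims.

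The figures assume equal variances over time, six analysed dyads in every playgroup, a normal approximation, and T2 and T3 taken one at a time. The covariance point is secondary and illustrative.

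**What to change.** In Statistical analysis, either fit the same mixed model with a common baseline mean across arms (no condition effect at baseline), or analyse T2 and T3 as outcomes with the child's baseline value and its interaction with time as covariates. Report the T2 and T3 contrasts.

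In Sample size and power, state which SDs are single-occasion and which are SDs of change, give the source of the discretionary-food SD, and note that Table 2 is conservative under baseline adjustment where single-occasion SDs were used.

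As a secondary step, allow an unstructured within-child covariance over the three visits, since T1 to T2 is 10 weeks and T1 to T3 about 8 months.

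The cost is a few sentences and a few extra parameters, with 360 to 480 children to estimate them. No new data are needed.
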